#### Secondary end points (outcomes)

The partial response rate is determined by the proportion of patients that have a ≥ 30% decrease of the sum of the longest perpendicular marker lesion diameters;The duration of the time to recurrence of NMIBC, in which patients who have continued metformin treatment after the study will be compared to those who did not. Patients will be followed for a maximum duration of 5 years. In case of a complete response; the time to recurrence is the duration of the complete response. In case of a partial response, no response or progressive disease, this is the time to recurrence after resection of the marker lesion;The number of grade 1–4 and grade 5 (fatal) NCI Common Terminology Criteria for Adverse Events Version 4.03 (CTCAE) events during treatment with metformin. All patients will be evaluable for toxicity from the time of their first treatment with metformin.

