## Methods/design

### Overall study design

This ‘*Phase II study of oral metformin for intravesical treatment of non-muscle-invasive bladder cancer*’ (TROJAN) study is a nonrandomized, open-label, multi-centre phase II clinical trial with oral metformin treatment in patients with intermediate-risk NMIBC. Patients will be enrolled at four hospitals in The Netherlands (the Amsterdam UMC in Amsterdam, the Jeroen Bosch Ziekenhuis in ‘s-Hertogenbosch, the RadboudUMC in Nijmegen and the Sint Franciscus Hospital in Rotterdam). This is a marker lesion study, meaning that in NMIBC patients undergoing TURB, a marker lesion will be deliberately left in the bladder. Patients will be treated with metformin for 3 months. Subsequently, the response on the marker lesion will be determined in a second TURB and the marker lesion is resected or (in case of a complete response) the area of the former marker lesion will be biopsied. After the second TURB, patients may choose to continue with metformin treatment.

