### Trial end points

#### Primary end points (outcomes)

The primary outcome is the complete response rate after 3 months of treatment with metformin. Evaluable patients are those who have received at least 500 mg metformin twice daily for one week and who undergo a cystoscopy for marker lesion removal. Primary study parameters are:
Complete response: complete disappearance of the marker lesion, as confirmed by negative biopsy at the marker lesion site, the absence of new tumours at other sites and a negative bladder washout cytology;No response: marker lesion persistence or the appearance of new lesions with stage T1 or less.

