## Discussion

The design of the study protocol we present here comes with several strengths; To the best of our knowledge, this is the first clinical trial that investigates the treatment of non-muscle invasive bladder cancer with oral metformin. The marker lesion procedure allows intra-patient assessment of tumour response to metformin before exposing patients to this new treatment modality in a large phase 3 study. Some limitations of the study design are; the fact that the marker lesion procedure may be a hurdle for rapid patient inclusion. The ideal application of metformin in non-muscle invasive bladder cancer may not be in ablating lesions but in chemoprevention of recurrences, a treatment indication for which a marker lesion study is not the appropriate design. In non-muscle invasive bladder cancer, chemoprevention rather than chemoresection is sought for as replacement of the current standard of bladder installations with chemotherapeutic drugs of BCG.

Overall there is a solid foundation of preclinical studies that warrants a clinical trial to explore the potential role of metformin in the management of NMIBC.

If positive, this phase II trial could legitimate phase III trials in intermediate- and possibly even high-risk NMIBC patients. In the best-case scenario, these trials will show that adjuvant metformin is more effective than adjuvant BCG/mitomycin and will, therefore, render intravesical BCG/mitomycin treatment obsolete (economic evaluation, scenario 1) and also extend the safe interval between cystoscopic surveillance (economic evaluation, scenario 2), in which case the potential savings can be added. In other scenarios, metformin may be non-inferior to BCG/mitomycin, but extending the interval between cystoscopic surveillance may not be safe. In that case, only the savings from scenario 1 apply. In brief, the nature of the proposed oral metformin treatment offers various cost-saving opportunities compared with the current standard of care for NMIBC.

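### The time-to-recurrence comparison sets patients who chose to continue metformin against those who did not, with a clock that depends on response, so it cannot be read as a metformin effect

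*Protocol article*

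**What the plan says.** The trial is described under Overall study design as a "nonrandomized, open-label, multi-centre phase II clinical trial with oral metformin treatment". Every patient takes metformin for 3 months, and the marker lesion response is then determined at a second TURB. The same section says how the two later groups arise: "After the second TURB, patients may choose to continue with metformin treatment".

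Under Secondary end points, time to recurrence is the outcome in which "patients who have continued metformin treatment after the study will be compared to those who did not", with follow-up of at most 5 years. The clock is given in two parts. For complete responders: "In case of a complete response; the time to recurrence is the duration of the complete response". For everyone else: "In case of a partial response, no response or progressive disease, this is the time to recurrence after resection of the marker lesion".

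Under Primary end points, new tumours seen at the 3-month cystoscopy rule out a complete response and fall in the other category: "No response: marker lesion persistence or the appearance of new lesions with stage T1 or less".

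**The concern.** The groups are formed by a choice made after treatment, with knowledge of the outcome of that treatment. Response and tolerability can each influence whether a patient continues, and each may also be related to later recurrence. A difference between the groups would then reflect who chose to continue as much as what metformin did. Nor is there an untreated group: all patients have had 3 months of metformin, so even an unbiased comparison would address only continuing versus stopping.

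The clock adds a second problem. Its origin is fixed for patients without a complete response and left open for complete responders. If response is also related to continuing, a difference in origin carries over into the comparison.

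The result may well be used. The Discussion says "The ideal application of metformin in non-muscle invasive bladder cancer may not be in ablating lesions but in chemoprevention of recurrences", and this is the only between-group comparison of later recurrence in the trial. The Economic evaluation section plans a model if the results suggest that metformin prolongs response duration.

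**Working it through.** **The plan's own figure.** None is given for time to recurrence. The sample size of 49 belongs to the primary endpoint and reproduces there: for 30% versus 50% response, requiring at least 22 responses in 49 gives an exact upper-tail alpha of 0.0195 and power of 0.804. It says nothing about the recurrence comparison.

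**1. Confounding by response.** The inputs are assumptions; the documents give none of them, except that 50% is the response rate the trial hopes to establish. Continuing has no effect. Complete response (CR) rate 50%. Recurrence hazard in CR is half that in non-CR. 80% of CR and 30% of non-CR continue.

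- Continuers: CR 0.5 × 0.8 = 0.40, non-CR 0.5 × 0.3 = 0.15, total 0.55. Share in CR: 0.40/0.55 = 73%.
- Non-continuers: CR 0.10, non-CR 0.35, total 0.45. Share in CR: 0.10/0.45 = 22%.
- Mean relative hazard at the start, continuers: (0.40 × 0.5 + 0.15 × 1)/0.55 = 0.636.
- Mean relative hazard at the start, non-continuers: (0.10 × 0.5 + 0.35 × 1)/0.45 = 0.889.
- Ratio: 0.636/0.889 = 0.72.

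Cox fits to large simulated samples with 5-year censoring and a non-CR hazard of 0.35 per year give about 0.71. Stratifying the same data by CR returns 0.99.

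**2. Sensitivity to the assumed choice.** The same formula, with the other inputs unchanged:

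| Continue, CR / non-CR | Starting hazard ratio, true effect none |
|---|---|
| 80% / 30% | 0.72 |
| 70% / 30% | 0.65/0.85 = 0.76 |
| 50% / 50% | 1.00 |
| 40% / 60% | 0.80/0.70 = 1.14 |

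Across a wider set (CR rate 30–50%; prognostic hazard ratio 0.7, 0.5 or 0.3; 70% versus 30% or 80% versus 20% continuing), the simulated hazard ratio runs from 0.88 down to 0.49. The size is therefore uncertain, and the sign depends on who continues.

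**3. How continuing is judged.** The article gives no time point. If a continuer were a patient with at least 6 months of use, with stopping at 0.5 per year and recurrence at 0.35 per year (all assumed, response playing no part), only patients free of recurrence for 6 months could qualify, and the hazard ratio would be about 0.51 with no true effect. Classifying the same patients without regard to later recurrence gives about 1.0.

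**4. The clock.** Non-CR patients start at resection of the marker lesion, at the second TURB. For CR patients, the duration of the response could start when the response is established at the second TURB, or at some point in the 3 months before. The origin may thus differ by 0 to 3 months. With the shares from step 1, a full 3 months would lengthen mean time in continuers relative to non-continuers by 3 × (0.73 − 0.22) = 1.5 months.

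**5. Information available.** Events for a hazard ratio of 0.5 with 80% power and two-sided 5%, groups equal: 4 × (1.96 + 0.84)² / (ln 0.5)² = 4 × 7.85/0.480, which rounds up to 66, more than the 49 patients. With 30 events the power is about 48%; if all 49 recur, about 68%. The 95% interval with 30 events multiplies and divides the estimate by exp(1.96 × 2/√30) = 2.05.

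**The case against.** The strongest reply is that no formal claim is planned. Statistical methods names no test or power for this outcome, the Discussion concedes that a marker lesion study is not the right design for chemoprevention, and the economic model is called preliminary. An article may also leave adjustment and operational definitions to the full protocol. That stands as far as missing detail goes, and such gaps are not the point here. What remains is what the article does state: a comparison of self-selected groups, without a caveat about that selection, and a clock worded differently by response.

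Four stronger readings are tempting and are not supported.

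- *The comparison must favour metformin.* Nothing in the documents says who will continue; step 2 shows that the sign can reverse.
- *Immortal time bias is built in.* It arises only if continuing is judged on later use. The text does not say so, and it places the choice after the second TURB.
- *Starting at the second TURB causes the bias, or loses recurrences seen on treatment.* For continuing versus stopping, that is the proper origin, because the choice is made then. New tumours at 3 months are not events in this outcome, but they count as no response in the primary endpoint, so they are not lost.
- *The 5–20% quoted in the Background sizes those tumours.* That range concerns solitary tumours 4 weeks after a supposedly complete resection. This trial requires at least two lesions and looks at 3 months, so the range does not carry over.

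**Conclusion.** The point holds in a limited form. As stated, the comparison is confounded by a choice made when response and tolerability are known, and its time origin is not clearly the same for complete responders and others. It cannot support a statement about metformin's effect on recurrence. The apparent hazard ratio of about 0.71 under no effect is an illustration. It rests on assumed response, prognosis and continuation rates, and it moves to 1.0 if continuing is unrelated to response and above 1 if non-responders continue more often. Immortal time would add to the bias only under a definition that the article does not give. This is a secondary endpoint and the primary analysis is untouched, so the change is advisable rather than essential.

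**What to change.** - Define the two groups by the continuation decision recorded at the second TURB, whatever the patient takes later.
- Start the clock at the second TURB for every patient, complete responders included.
- Present the comparison stratified by complete response versus not.
- Label it descriptive, as continuing versus stopping after 3 months of metformin in all patients, with no causal reading. Stratifying removes confounding by response only; tolerability and other reasons for the choice remain. Further covariates are not advised with so few patients.
- Report new non-marker tumours at the 3-month cystoscopy separately, as a simple proportion. The primary endpoint merges them with persistence of the marker lesion.

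The cost is mainly wording. The continuation decision must be recorded, and the article's visit table does not list it. The stratified interval will be wide: at most 49 patients contribute, and even the unstratified interval with 30 events spans a factor of about two either way. No extra visits, procedures or patients are needed.

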#### Exploratory end points (outcomes)

The immunohistochemical expression of tumour biology markers such as AMPK and TSC2 before and after metformin treatment.Trough metformin levels in serum and metformin levels in a sample of urine collected over 12 h in samples taken after 6 weeks and after 3 months of metformin treatment. These levels will be pharmacokinetically analysed and correlated to the marker lesion response data and the patient’s toxicity data.

### Participants

In brief, this trial will enrol 49 eligible patients with NMIBC. All inclusion and exclusion criteria are listed in Table 1. The sample size is based on a power analysis described under Statistical methods.

**Table 1 Tab1:** Inclusion and exclusion criteria

Key inclusion criteria	
• Age ⩾18 years. • Patients with primary or recurrent multiple histologically confirmed Ta or T1 (non-muscle invasive), G1 or G2 (low-grade) urothelial carcinoma of the bladder with no evidence of carcinoma in situ. • Patients must have at least 2 lesions, but no more than 10. • The resected lesions must contain detrusor muscle to confirm a Ta/T1 disease. • All visible lesions must be completely removed by transurethral resection at entry to the study, except for an untouched marker lesion measuring 0.5–1.0 cm in its greatest dimension. • Bimanual examination immediately following transurethral resection under anaesthesia should be carried out and no mass should be felt. • Adequate renal function (creatinine < 150 μmol/L and/or an eGFR > 60 ml/L). • Adequate liver function (bilirubin < 1.5 times upper limit of normal, ALAT or ASAT < 2.5 the upper limit of normal). • Eligible patients must be fully informed of the investigational nature of the study and written signed informed consent must be obtained prior to any study specific investigations. • Mentally, physically, and geographically able to undergo treatment and follow up.	
Key exclusion criteria	
• Patients having muscle-invasive disease (stage T2 or greater) or CIS. • Patients with grade 3 (high-grade) tumours. • Patients with diabetes mellitus receiving metformin or having received metformin in the past 6 months. • Patients who have received intravesical treatment (chemotherapy or immunotherapy) within the last 3 months. • Patients that are currently receiving other anti-cancer therapy. • Patients with existing urinary tract infection or recurrent severe bacterial cystitis. • Patients that need to be treated with a transurethral catheter. • Patients with urogenital tumours with histology other than urothelial carcinoma (i.e., squamous cell or adenocarcinoma) or with urothelial carcinoma involving the upper tract or the prostatic urethra. • Patients with a history of other primary malignancy (other than squamous or basal cell skin cancers or cone biopsied CIS of the uterine cervix or prostate carcinoma treated curatively with normal PSA values at inclusion) in the last five years. • Patients with active, uncontrolled impairment of the renal, hepatobiliary, cardiovascular, gastrointestinal, urogenital, neurologic or hematopoietic systems that, in the opinion of the investigator, would predispose to the development of complications from the administration of metformin. • Patients who are using loop diuretics, cimetidine, ranitidine, cetirizine, trimethoprim, vandetanib, kinidine and/or anti-HIV medication (due to drug interactions), for which no reasonable alternative is available. • Women who are pregnant or lactating. Individuals of reproductive potential may not participate unless agreeing to use an effective contraceptive method for themselves and/or their sexual partner. • Patients with ECOG-WHO performance status of 3 or 4. • Patients with a known history of alcohol abuse. • Patients with a known hypersensitivity to metformin. • Patients who in the investigator’s opinion, cannot comply with provisions of the protocol or do not understand the nature of the study.	

Abbreviations: *CIS* carcinoma in situ, *ECOG* Eastern Cooperative Oncology Group, *eGFR* estimated glomerular filtration rate, *HIV* human immunodeficiency virus, *PSA* prostate-specific antigen, *WHO* World Health Organisation

### Dose of study drugs and dose adjustments

All patients will receive metformin orally in a starting dose of 500 mg once daily and, if well tolerated, this will be increased to 500 mg twice daily in the second week, 1000 mg twice daily in the third week and, with a good renal function, eventually to a maximum of 3000 mg per day. This highest metformin dose is reserved to those with an estimated glomerular filtration rate (eGFR) of ≥60 mL/min to reduce the risk of lactic acidosis. Based on toxicity data from patients with T2DM, we expect that 2550 mg of metformin (850 mg three times daily) is a realistic maximum tolerable dose in most patients with an eGFR of ≥60 mL/min [27]. This dosing schedule conforms with the metformin label from the US Food and Drug Administration in the treatment of T2DM and the purpose of the stepwise dose increase is to reduce gastro-intestinal side effects [28]. Doses will be reduced for haematological and other adverse events. Dose adjustments are to be made according to the system showing the greatest degree of toxicity. Examples of metformin dose adjustments due to frequently occurring adverse events are shown in the Additional file 1**.**

### Toxicity monitoring and adverse events

Adverse events will be graded using the CTCAE version 4.03. The major adverse effects of metformin, which may limit the maximum tolerable dose, are of gastro-intestinal nature, such as nausea, vomiting, diarrhoea, abdominal discomfort and loss of appetite. A rare but serious adverse event that can occur during metformin treatment is lactic acidosis [29]. This life-threatening condition is caused by accumulation of metformin. Risk factors include a combination of old age, doses over 2000 mg per day and renal impairment, either due to chronic renal impairment or due to acute renal failure as the result of dehydration, shock or the intravenous administration of iodinated contrast agents. The estimated prevalence of lactic acidosis is < 5 cases per 100,000 patient years [30].

### Study visits

Patients with NMIBC will visit their hospital of inclusion once for TURB and additional eligibility screening (see in- and exclusion criteria). Once enrolled in the study, patients will undergo a study visit after 6 weeks, when blood will be drawn and urine will be collected for analysis of hematologic, hepatic, renal, and chemistry parameters and for pharmacokinetic analyses. After 3 months, these procedures will be repeated and patients will undergo a cystoscopy and resection of their marker lesion if still present or a biopsy of the marker lesion site. Specifics for each study visit are provided in Table 2. Patients will have a telephone appointment with their study physician before every metformin dose increase. For most patients, these phone calls will thus be scheduled after weeks 1, 2, and 3.

**Table 2 Tab2:** Timeline, study treatment, study visits and medical procedures

Required Investigations	Prestudy	Telephone calls	6 weeks after start treatment	3 months after start treatment (end of treatment)
Written informed consent	X			
Demographics	X			
Overall medical history	X			
ECOG/WHO performance status	X	X	X	X
Adverse events		X	X	X
EORTC QLQ-NMIBC24	X		X	X
SF-36 quality of life	X		X	X
Medication diary		X	X	X
Physical:				
Physical examination	X		X	X
TURB	X			X
Haematology:				
Complete blood counts	X		X	X
PT, APTT	X			
Clinical chemistry:				
Renal function	X		X	X
Liver function	X		X	X
Serum glucose	X		X	X
HbA1c	X			X
Insulin	X			X
IGF-1	X			X
IGF binding protein-3	X			X
Other Investigations:				
Metformin concentration in serum			X	X
Metformin concentration in urine			X	X
Urinalysis	X		X	X
Pathological review of biopsies	X			X

Abbreviations: *ECOG* Eastern Cooperative Oncology Group, *IGF* insulin growth factor, *WHO* World Health Organisation

### Therapy response assessment

The cystoscopic assessment of marker lesions is generally considered to be relatively insensitive to inter- and intra-observer heterogeneity. However, in order to pursue the most unbiased and reproducible analysis possible, cystoscopic video images of the marker lesion before and after metformin treatment will be stored and independently scored by three independent urologists that are blinded to the timing of the image acquisition (pre- or post-treatment). Differences in opinion will be discussed and, if necessary, solved by a fourth independent urologist. The urologist will judge whether there is a complete response (disappearance of the marker lesion), partial response (at least a 30% decrease of the sum of the longest perpendicular marker lesion diameters) or no response. Partial responses will be determined using the 8-mm span of the cutting loop for reference. We will perform immunohistochemical staining of tumour biology markers such as AMPK and TSC2 to investigate the molecular response of the marker lesion to metformin.

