#### Exploratory objectives

The effect of metformin on tumour biology markers in biopsies or tumour resection tissue taken before and after study treatment;The pharmacokinetic analysis of metformin levels in urine and serum;In case of promising results: a preliminary economic evaluation to estimate potential cost savings that could be achieved using metformin in NMIBC patients.

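### The before/after staining cannot show the molecular response of the marker lesion: that lesion has no pre-treatment tissue, and complete responders have no post-treatment marker tumour

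*Protocol article*

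**What the plan says.** Three places in the protocol article describe the staining. Exploratory objectives asks for the effect of metformin on "tumour biology markers in biopsies or tumour resection tissue taken before and after study treatment". Exploratory end points gives the outcome as "The immunohistochemical expression of tumour biology markers such as AMPK and TSC2 before and after metformin treatment". The last sentence of Therapy response assessment goes further and says that the staining is done "to investigate the molecular response of the marker lesion to metformin".

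Three other places decide what tissue exists:

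- Table 1 under Participants has everything visible resected at entry "except for an untouched marker lesion measuring 0.5–1.0 cm in its greatest dimension". The same table states: "Patients must have at least 2 lesions, but no more than 10".
- Primary end points defines complete response as "complete disappearance of the marker lesion, as confirmed by negative biopsy at the marker lesion site", together with no new tumours elsewhere and negative washout cytology.
- Study visits provides at 3 months for "resection of their marker lesion if still present or a biopsy of the marker lesion site".

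No section says that the pre-treatment sample comes from a different lesion, or that post-treatment marker tumour exists only in some of the patients.

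**The concern.** A response of the marker lesion is a change within one lesion, which needs tumour from that lesion at both times. The design never supplies such a pair. It supplies a resected lesion at entry and, if any marker tumour is left, the marker lesion at 3 months.

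Two things then enter the before/after difference that are not a drug effect on the marker lesion. One is the difference between two lesions of the same patient. The other is selection by outcome, because patients whose marker lesion has vanished cannot contribute tumour. The trial has no untreated arm against which either could be judged. A difference in staining could be reported as drug action when it partly reflects which lesion was sampled. An absent difference would say nothing about the lesions that disappeared.

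**Working it through.** **Inputs.** 49 evaluable patients, with complete response rates of 50% (hoped for) and 30% (to be rejected), from Statistical methods. 2 to 10 lesions per patient and an untouched marker lesion, from Table 1. The definition of complete response, from Primary end points.

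**The plan's own figure.** The article gives no number for the staining. Its sample size does reproduce with two-sided alpha 0.05 and 80% power by the normal approximation: (1.960 + 0.842)² × 0.5 × 0.5 / (0.5 − 0.3)² = 7.849 × 0.25 / 0.04 = 49.06. The base of 49 is therefore taken as it stands.

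**Step 1: pre-treatment tissue.** With k lesions, k − 1 are resected and one is left untouched. That gives 2 − 1 = 1 to 10 − 1 = 9 resected lesions per patient, and none of them is the marker lesion. Within-lesion before/after pairs: 0 of 49.

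**Step 2: post-treatment marker tumour.** A complete responder has none, by definition. The expected number without complete response is 49 × (1 − CR):

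- CR = 50%: 49 × 0.5 = 24.5 (binomial 95% range 18 to 31)
- CR = 30%: 49 × 0.7 = 34.3 (binomial 95% range 28 to 40)

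**Step 3: why these are upper limits.** The other class in Primary end points reads "No response: marker lesion persistence or the appearance of new lesions with stage T1 or less". A patient whose marker lesion has gone but who has a new tumour elsewhere is therefore not a complete responder, and the same holds for positive cytology. Such patients are counted in step 2 but have no marker tumour to stain. The article gives no figure for their number, so the expected counts are at most about 24–25 and about 34.

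**Step 4: what the difference measures.** In a patient with residual tumour,

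observed difference = (marker lesion after − marker lesion before) + (marker lesion before − resected lesion before).

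The first bracket is what Therapy response assessment claims to study. The second is a between-lesion difference. Marker lesion before is never measured, so the two brackets cannot be separated.

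**Step 5: who can supply a between-lesion yardstick.** Two entry lesions can be stained only if k − 1 ≥ 2, that is k ≥ 3. Patients with exactly two lesions are eligible and cannot supply it.

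**The case against.** The strongest reply is that only one phrase is at fault. Exploratory objectives and Exploratory end points never say that both samples come from the marker lesion, and both can be read as a within-patient comparison across lesions. An article also commonly leaves the choice of block, the formation of pairs and the analysis set to the full protocol or the analysis plan. This stands as far as the missing details go, and they are not criticised here. It does not rescue the phrase, since no later document can create pre-treatment tissue from a lesion left untouched.

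A second reply also stands in part. Random differences between lesions of one patient add noise to a paired mean. They bias it only if marker lesions differ systematically from resected ones. The 0.5–1.0 cm window applies to the marker lesion alone and could cause such a difference, but nothing in the article shows that it does.

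A reader might infer that the post-treatment sample consists only of treatment failures. The article does not support this. Partial responders, with at least a 30% decrease, still have marker tumour, although the primary endpoint counts a persisting lesion as no response.

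A reader might also want to put a size on how far the selection understates the marker change. That needs a correlation between marker change and response and a distribution for the change. The article gives neither, so no such figure is offered.

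**Conclusion.** The contradiction is in the text. An untouched marker lesion and a negative site biopsy in complete responders mean that the staining cannot show how the marker lesion itself responded. What can be compared is a lesion resected at entry with the residual marker lesion, in patients who have residual marker tumour, partial responders included.

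The size is 0 of 49 within-lesion pairs, and expected cross-lesion pairs of at most about 24–25 at a 50% complete response rate and about 34 at 30%. These counts assume all 49 evaluable patients, usable tissue from every resection, and the definition of complete response in Primary end points. The more complete responses there are, the fewer and the more selected the pairs.

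It would go too far to conclude that the staining must miss a working mechanism, or that it is certainly biased. What is established is that it cannot be read as the sentence reads it. The consequence is small: the endpoint is exploratory, and the primary analysis, the sample size and the stopping rule after 13 patients do not depend on it.

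**What to change.** 1. In Exploratory objectives, Exploratory end points and Therapy response assessment, describe the comparison as a lesion resected at entry against the residual marker lesion, in patients with residual marker tumour. Remove the claim that it shows the molecular response of the marker lesion.
2. Where two or more lesions were resected at entry, stain two of them and judge the before/after difference against the difference between these two. This gauges ordinary variation between lesions. It does not detect a systematic difference between marker and resected lesions, and it cannot be done in patients with only two lesions.

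Making baseline expression in complete responders versus the others the main staining analysis is not recommended. It would replace the stated objective, the effect of metformin on the markers, with a question about prediction. It would also keep the mismatch, because expression in a resected lesion would be set against the response of another one.

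The cost is a change of wording, some extra staining of tissue already in hand, and a weaker mechanistic claim. No additional biopsy is needed.
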